#### Secondary endpoints

Incidence of acute kidney injury as defined by RIFLE criteria (in hospital and at midterm [3 months]) (see Appendix: Table 4)Relative change of calculated GFR (by cystatin C) up to the third postoperative dayGlycocalyx shedding (syndecan 1, hyaluronan) at days 0, 1 and 3Glomerular damage as measured by neutrophil gelatinase-associated lipocalin at days 0, 1, 3 and 90Length of ICU and hospital stayNecessity and duration of renal replacement therapyPresence of pruritus at day 90

#### Further objectives and variables

We also want to investigate the effect of the fluid therapy on the thrombocyte function and coagulation as measured using the Multiple Platelet Function Analyzer (Multiplate; Roche Diagnostics, Mannheim, Germany), Platelet Function Analyzer (PFA 100; Siemens Healthcare, Erlangen, Germany) and rotational thrombelastometry (ROTEM; Tem international GmbH, Munich, Germany). Also we are interested in the life quality after the operation evaluated by standardized interviews. Furthermore, we will collect the following data:Intraoperative blood loss, urine output and fluid amountThe laboratory chemical course of creatinine and urea, starting before surgery up to the third postoperative day and at 90 days (visit 5)The laboratory chemical course of serum albumin, starting presurgically up to the third postoperative dayMortalityDementia screening (Mini Mental State Examination) on the day of screeningDelirium screening (Nursing Delirium Screening Scale) postoperatively in the recovery room and at days 1 and 3Life quality assessment preoperatively and at day 90 (activities of daily living, instrumental activities of daily living)Effect on thrombocytes and coagulation measured by ROTEM, PFA 100) and Multiplate at day 0Incidence of adverse events and SAEs

## Methods/Design

In this single-center, open-label, randomized, comparative trial, we will investigate two parallel patient groups, comparing HA (test drug) versus HES (comparator). Ethical approval of this trial was obtained from the ethics committee of the Ludwig Maximilians University of Munich (reference number 311-11). The confirmatory statistical analysis is based on a leading surrogate parameter of renal function, with the aim of establishing a recommendation for therapy optimization. Because both investigational medicinal products (IMPs) are licensed for volume replacement in the perioperative setting in this trial, it is a phase IV trial. However, the clinical aim corresponds to that of a confirmatory phase IIb or III trial.

Randomization will be performed by stratifying participants by type of surgical procedure (ileum conduit or neobladder) to balance allocation to treatment groups with respect to this risk factor for postoperative renal dysfunction.

After randomization, each patient will receive the allocated volume replacement treatment according to the current prescribing information up to the seventh operative day. The patient should be kept on the allocated infusion solution during the first 90 days after operation if further volume replacement therapy becomes necessary, if not contraindicated, and if manageable.

A detailed schedule of study activities, and the treatment algorithm to be used for fluid management in both treatment arms are provided in the Appendix: Tables 1, 2 and 3.

### Anesthetic management

All patients will receive thoracic epidural anesthesia in combination with general anesthesia before surgery. Patients with contraindications to neuraxial procedures (e.g., dual platelet inhibition) will receive general anesthesia and postoperative patient-controlled analgesia with piritramide. The anesthetic technique used will be standardized. Anesthesia will be induced with propofol (2 mg/kg), sufentanil (0.4 mg/kg) and rocuronium (0.6 mg/kg) and maintained with propofol and remifentanil or sevoflurane in patients with certain conditions (e.g., cardiopulmonary diseases). After surgery, the epidural will be maintained for at least 3 days and will be combined with acetaminophen, non-steroidal anti-inflammatory drug and an opioid (piritramide) if needed. Intraoperative hemodynamic monitoring will be performed with a Vigileo monitor with FloTrac sensor (Edwards Lifesciences, Irvine, CA, USA). After randomization, patients will receive either HA or HES from one of the investigators according to an algorithm (see Appendix).

### Postoperative care

American Society of Anesthesiologists Physical Status (ASA) classification I and II patients without cardiopulmonary diseases or cerebral insufficiency will be transferred directly from the recovery room to the general ward. ASA classifications III and IV patients or those with perioperative complications will be transferred from the operating room to the ICU for at least 1 day. All patients will receive early postoperative enteral feeding without a nasogastric tube as well as early mobilization. All patients will be visited by in-hospital postoperative pain management service staff daily.

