#### Randomization and stratification

This trial is designed as an open-label trial. Randomization will be performed at the Institute for Medical Informatics, Biometry and Epidemiology (IBE) of the University of Munich, and the treating physicians will be informed about the treatment arm to which a patient is assigned.

Randomization to both treatment arms will be performed in a ratio of 1:1. The randomization technique is based on randomized, balanced blocks with random block length. The procedure considers stratification by type of surgical procedure (ileal conduit or neobladder). The IBE will provide an internet-based randomization tool (Randoulette), which chooses the colloid treatment group for a new patient fulfilling the eligibility criteria and having signed the informed consent. Randoulette will register the patient by the patient’s pseudonym or screening number, sex, year of birth and stratum (ileal conduit or neobladder) before the allocated colloid treatment group is provided.

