### Statistical planning and analysis

#### Statistical analyses

The primary efficacy analysis statistically tests superiority of HA versus HES at an α significance level of 5 % (two-sided, simultaneously testing both sides at a level of 2.5 %) with respect to the primary endpoint.

The primary endpoint is expected to be non-normally distributed. After logarithm transformation, the primary endpoint may not be normally distributed. Thus, the corresponding statistical null hypothesis is the hypothesis that the distribution functions of the endpoint in the HA group and the HES group are equal and will be tested non-parametrically with the Mann-Whitney-Wilcoxon test to detect directed differences of the distributions. The Mann-Whitney-Wilcoxon test will be applied. The one-sided *p* value will be calculated, if possible, using Fisher’s exact test.

The primary endpoint adjusts in a specific way for the preoperative cystatin C values. At the planning stage, the Mann-Whitney-Wilcoxon test will be applied in the stratified version by type of surgical procedure (ileal conduit or neobladder). If adjustments of stratification are deemed necessary during the course of the trial, the trial protocol will be amended.

A fixed-sample design is planned. Changes of trial design, if necessary or advisable, resulting from an interim analysis without significance testing (no αspent) had to keep the prespecified significance level. In that case, the Brownian motion will be used for modeling the primary test statistic based on the accumulating data as a stochastic process (see next section).

The distributions will be described at all time points by median, minimum, maximum and quartiles separately for both the HES and HA groups.

The primary statistical analysis will be based on the intention-to-treat (ITT) principle.

Analysis of all secondary endpoints and of patient characteristics will be descriptive. Descriptive comparisons will be conducted with the *t* test or, in the case of deviations from the normal distribution, with the Mann-Whitney-Wilcoxon test, or with Fisher’s exact test in case of a binary outcome.

Safety data will be analyzed descriptively in the two groups at least every 12 months.

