#### Power considerations and sample size calculation

Three parameters will influence the sample size of the study, in which we will use the Mann-Whitney-Wilcoxon test for the statistical decision based on a fixed-sample design: the level of significance, the power of the two-sided test and the probability that an observation X_AlbuCyst_ in the HA group is less than an observation X_VoluCyst_ in the HES group. For sample size planning, no stratification and approximately normally distributed data for log-transformed cystatin C values and calculated log-transformed GFR values are assumed. The location parameter and standard deviation of cystatin C at baseline are assumed to be 0.9 mg/L and 0.2 mg/L, respectively, based on the publication by Evangelopoulos and colleagues [23]. Thereby we consider the older patient groups and greater variability because subgroups are pooled and study patients did not represent a healthy population.

For sample size calculation, the value of 0.2222 for the standard deviation of the difference at day 90 minus baseline of the log-normal transformed cystatin C values is specified in both treatment groups. There are two arguments for this specification. First, the value is suggested to be conservative in the four groups (two treatments times two measurement time points) considered in the statistical analyses. Second, adjusting for baseline values by using cystatin C values at day 90 relative to the same patients’ value at baseline is suggested to reduce rather than to increase the standard deviation.

An increase of the GFR by the factor 1.2 due to HA compared with HES would be clinically meaningful and worthwhile to be detected as statistically significant difference at a two-sided type I error level of α = 5 % with a statistical power of 1 − β = 80 %. For the interpretation of the increase of the GFR by the factor 1.2 consider, for example, a patient with a Cystatin C value of 0.9 mg/L. This value results in a calculated GFR at baseline between 86 and 87 ml/min. Then, the factor 1.2 would mean an increase of GFR at day 90 from 60 to 72 ml/min, from 65 to 78 ml/min, or from 70 to 84 ml/min.

The factor of 1.2 with respect to GFR transfers to the detectable difference of 0.1368 for the log-transformed (natural logarithm) Cystatin C values when using the conservative formula where the exponent is −1.333.

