## Appendix

**Table 1 Tab1:** Flowchart

Schedule of activities	Visit 1	Visit 2	Visit 3	Visit 4	Visit 5
	Screening day (day −1)	Day 0 (day of surgery)	Day 1	Day 3	Day 90
Informed consent	X				
Inclusion and exclusion criteria	X				
Demographic data	X				
Medical history (primary diagnosis)	X				
Pregnancy test for women of childbearing potential	X				
Mini Mental State Examination	X				
Life Quality Assessment (ADL, IADL)	X				X
Concomitant medications (diuretics)	X	X	X	X	X
Cystatin C, GFR, serum creatinine	X	X	X	X	X
ROTEM, Multiplate, PFA 100		X			
Randomization		X			
NGAL, syndecan 1, hyaluronan		X	X	X	
Study drug		X	X	X	
Blood products		X	X	X	
IV fluid amount		X	X	X	
Blood losses and urine output		X	X	X	
Nursing Delirium Screening Scale		X	X	X	
AEs and SAEs		X	X	X	X
Pruritus assessment					X

*ADL* activities of daily living, *AE* adverse event, *IADL* instrumental activities of daily living, *IV* intravenous, *NGAL* neutrophil gelatinase-associated lipocalin, *PFA 100* Platelet Function Analyzer 100, *ROTEM* rotational thrombelastometry, *SAE* serious adverse event2

**Table 2 Tab2:** Algorithm of infusions and transfusion in the operating room and intensive care unit

Hemodynamics	
ASA I and II patients without cardiac diseases or cerebral insufficiency:	
Stroke volume variation (SVV) <12 %	
Cardiac index (CI) > 2.5 L/min/m^2^	
MAD >60 mmHg	
ASA III and IV patients or patients with cardiac diseases or cerebral insufficiency:	
SVV <12 %	
CI >2.5 L/min/m^2^	
MAD >70 mmHg	
Central venous oxygen saturation >70 % or mixed venous oxygen saturation >65 %	
To reach the desired parameter:	
Start with infusion protocol (see below)	
If not successful within 15 minutes:	
Start with norepinephrine as first-choice vasopressor	
Infusion protocol	
Replacement of urine output with Ringer’s acetate solution in a 1:1 ratio	
Additionally, 500 ml of crystalloids for insensible sweating	
Replacement of blood and protein losses dependent on treatment assignment, with either HA 5 % or HES 6 % in a 1:1 ratio up to a transfusion trigger point or a maximum of 50 ml/kg/day	
Additionally up to 1500 ml of colloids for the protein loss into the third compartment

**Table 3 Tab3:** Transfusion protocol (in support of [24])

Red blood cells			
Hb (g/dl)	Risk factors	Transfusion	Evidence level
<6 g/dl	–	Yes	1c+
>6–8 g/dl	Adequate compensation, no risk factors	No	1c+
	Limited compensation or risk factors (cardiac diseases, cerebrovascular insufficiency)	Yes	1c+

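### ICU length of stay is compared without regard to ASA class, although ASA class alone sets a minimum ICU stay; the place named for the first delirium score also conflicts with the postoperative pathway

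*Protocol article*

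**What the plan says.** Secondary endpoints in the protocol article lists time spent in the ICU and in hospital. Postoperative care sets out two paths. ASA I and II patients free of cardiopulmonary disease and cerebral insufficiency "will be transferred directly from the recovery room to the general ward". The other path is for "ASA classifications III and IV patients or those with perioperative complications", who "will be transferred from the operating room to the ICU for at least 1 day". So there are two routes to the ICU: a preoperative class, and an event around surgery.

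Randomization and stratification names the type of urinary diversion as the only stratum. It also states: "This trial is designed as an open-label trial". Statistical analyses says: "Analysis of all secondary endpoints and of patient characteristics will be descriptive". It names the t test, the Mann-Whitney-Wilcoxon test or Fisher's exact test for these comparisons, with no stratification. The stratified Mann-Whitney-Wilcoxon test is planned for the primary endpoint only, by diversion type.

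Delirium appears under Further objectives and variables. The first score is placed in the recovery room, with later scores on days 1 and 3. Table 1 in the Appendix marks the "Nursing Delirium Screening Scale" on days 0, 1 and 3 and names no place.

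**The concern.** A patient in ASA class III or IV has an ICU stay of at least one day whichever colloid is given. An uncomplicated ASA I or II patient without the listed comorbidities has none. Spread in ICU stay that comes from this rule carries no information about the fluid. With about 50 patients per arm, ASA class may also be unevenly split by chance, and an unstratified comparison does nothing about that. A real difference can be hidden, or a chance one can look larger than it is.

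The delirium problem is one of consistency. If the first score is tied to the recovery room, it does not fit patients who go from the operating room to the ICU. Some of them go there because of complications that can arise after randomization. If the wording were followed literally, the score would be lost in higher-risk and complicated patients.

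**Working it through.** **The plan's own figure.** Inputs from the sample size section: GFR factor 1.2, exponent 1.333, SD 0.2222, two-sided 5%, power 80%, dropout 10%.

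- Difference: ln(1.2)/1.333 = 0.1368.
- P = Φ(0.1368/(0.2222·√2)) = 0.6683.
- Noether: N = (1.960 + 0.842)²/(12·0.25·0.1683²) = 92.4, so 47 per group and 94 in total.
- Enrolment: 94/0.90 = 104.4, so 105.

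All stated figures reproduce, and nothing below changes them.

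**Dilution of the ICU admission contrast.** The article gives no ASA mix and no complication rate, so these are assumptions: complications in 40% v 20% of patients, independent of ASA class, and a share f in ASA III/IV. Everyone in ASA III/IV is admitted, as is everyone with a complication. The admitted share is f + (1−f)·0.40 in one arm and f + (1−f)·0.20 in the other, a difference of (1−f)·20 points.

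If the comparison is stratified by ASA class, the III/IV stratum contributes nothing to admission, because all its patients are admitted in both arms. The test then rests on n = 47·(1−f) per arm in ASA I/II, at 40% v 20%. Power = Φ((0.20 − 1.96·√(2·0.3·0.7/n))/√((0.24 + 0.16)/n)).

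| f | Admitted | Difference | Power, unstratified | n per arm, ASA I/II | Power, stratified |
|---|---|---|---|---|---|
| 0 | 40% v 20% | 20 points | 56% | 47 | 56% |
| 0.2 | 52% v 36% | 16 points | 34% | 37.6 | 47% |
| 0.4 | 64% v 52% | 12 points | 22% | 28.2 | 37% |
| 0.6 | 76% v 68% | 8 points | 14% | 18.8 | 26% |

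Stratifying recovers part of the loss. It cannot recover the information in patients who are admitted by rule.

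**Length of stay.** This also varies beyond the first day, so the gain is smaller than for admission. A simulation on assumed rates with f = 0.4 gives power of about 31% for the unstratified test and 37% for the stratified one, with type I error near 5% for both. The level depends on the assumed distribution of stay. I repeated it with 40% v 20% complications and geometric extra days (mean 1 to 2 after a complication, 0.3 to 0.5 otherwise). That gave 23% to 27% unstratified and 28% to 33% stratified.

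**Chance imbalance in ASA class.** The standard error of the between-arm difference in the ASA III/IV share is √(2p(1−p)/47). It is 0.095, 0.101 and 0.103 for p = 0.3, 0.4 and 0.5. The 95% limits (×1.96) are 0.185, 0.198 and 0.202. With the one-day floor, one standard error is roughly 0.10 ICU days per patient, and 0.2 days is the edge of the 95% range. These slightly overstate the effect, since patients with complications would be admitted anyway.

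**Delirium.** No arithmetic applies. Further objectives and variables names the recovery room. Postoperative care takes some patients from the operating room to the ICU. Table 1 requires a day-0 score and is silent on place. The three statements can be made to agree, but as written the first two do not, and the third does not settle it.

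**The case against.** Several stronger readings are tempting, and the document does not support them.

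- *A reader might infer that ASA class alone decides ICU admission.* It does not. Perioperative complications are a second route and can respond to the fluid, and one day is a minimum, so later days can differ by arm. The contrast is diluted, not removed.
- *A reader might infer that the ICU comparison is biased.* ASA class precedes randomization, so it is balanced in expectation. Chance imbalance is already part of the sampling variance, and the unstratified test keeps its error rate.
- *A reader might take 0.2 ICU days as the expected spurious difference.* It is the edge of a 95% range on an assumed ASA mix. It also uses 47 per group, which is the number assessed at day 90; with the 50 to 55 enrolled per arm the range is a little narrower.
- *A reader might conclude that the day-0 delirium score is missing in the sickest patients.* The article does not say so: Table 1 schedules it on day 0 without a place, and the scores on days 1 and 3 are unaffected. Differential loss by arm is possible but not shown.

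It is also fair to say that a condensed article may leave the handling of ICU days to a fuller document, that secondary analyses are descriptive, and that delirium is only a further variable. This lowers the weight of the point. What stands is that the article names unstratified tests for an endpoint its own care pathway partly fixes, and that it names a place for the delirium score that does not fit that pathway. The complication route is also undefined in the article and, in an open-label trial, leaves room for judgement.

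**Conclusion.** The point holds as a minor one. The unstratified comparison of ICU length of stay carries avoidable variance from a baseline class. On the assumed rates with 40% of patients in ASA III/IV, stratifying is worth about 5 to 8 percentage points of power for length of stay and about 15 for ICU admission (22% to 37%). Power stays low in every case, so the endpoint remains descriptive. These sizes rest on assumed complication rates, ASA mix and stay distributions; the direction does not.

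The delirium wording is a plain inconsistency between two sections that Table 1 leaves open. The primary endpoint, its test and the sample size are not affected.

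**What to change.** 1. Compare ICU length of stay with a test stratified by ASA class (I/II v III/IV), for example the stratified Mann-Whitney-Wilcoxon test already planned, by diversion type, for the primary endpoint.
2. Report ICU admission among ASA I/II patients by arm as a supporting descriptive result. Say how ASA I/II patients with cardiopulmonary disease or cerebral insufficiency are counted, since the article gives no destination for them when they have no complication.
3. Do not subtract the first ICU day across the board. In patients admitted because of complications, that day may itself reflect treatment.
4. Reconcile Further objectives and variables, Postoperative care and Table 1, so that the first delirium score is taken at a common time point in the recovery room or the ICU, whichever the patient is in.

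The cost is wording. ASA class is already needed for the postoperative pathway and for the Table 2 algorithm. Patient care does not change.

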### Treatment groups

After screening and randomization, every patient is assigned to one of the two therapy arms:*VoluCyst study arm* (patients with cystectomy treated with HES): In this arm, patients receive 6 % HES 130/0.6 (Volulyte) perioperatively and up to the third postoperative day as the only colloid according to a treatment algorithm (see Appendix). The maximum dose according to the prescribing information is 50 ml/kg/day (e.g., 3500 ml for a patient with a body weight of 70 kg). Patients who require additional volume replacement therapy from day 3 until discharge will be treated primarily with HES, unless a contraindication to HES has emerged.*AlbuCyst study arm* (patients with cystectomy treated with HA): In this arm, patients receive 5 % HA (Humanalbin) perioperatively and up to the third postoperative day as the only colloid according to a treatment algorithm (see Appendix). Patients who require additional volume replacement therapy from day 3 until discharge will be treated with HA.

### Trial population and selection criteria

Patients will be screened for eligibility by using the surgery schedule. Patients who seem to be eligible for study participation based on their diagnosis are screened according to the inclusion and exclusion criteria. Patients who fulfill these criteria are informed about the present study.

#### Inclusion criteria

Subjects must meet all of the following inclusion criteria to be eligible for enrolment into the trial:Patients (male and female) aged 18–85 yearsPatients undergoing cystectomy with urinary diversion using an ileal conduit or neobladder procedureAbility to follow study instructions and likely to attend and complete all required visitsWritten informed consent provided

#### Exclusion criteria

Subjects presenting with any of the following exclusion criteria may not be included in the trial.

##### General exclusion criteria

Unfavorable prognosis (e.g., palliative surgical care in cases of obstruction of the efferent urinary tract)Evidence of metastatic diseaseBleeding tendency or platelet dysfunctionPreoperative creatinine clearance <30 ml/minPreoperative chemotherapy with nephrotoxic drugs (e.g., cisplatin)Application of >1000 ml of colloid solution within the 24 h before surgical interventionPhysical or acute medical condition, psychiatric condition or laboratory abnormality that, based on the investigator’s decision, may put the patient at risk, may confound the trial results or may interfere with the patient’s participation in this clinical trialHistory of hypersensitivity to the investigational drug or to drugs with a similar chemical structureHistory of uncontrolled chronic disease or a concurrent clinically significant illness or medical condition that, in the investigator’s opinion, would contraindicate study participation or compliance with protocol-mandated proceduresKnown or persistent abuse of medications, drugs or alcoholSimultaneous participation in another clinical trial or participation in any clinical trial involving an IMP within 30 days before provision of written informed consent for this trial

